###### Strengths and Difficulties Questionnaire

At T4, mothers and fathers will provide an indication of their child's social-emotional and behavioral adjustment using the 2- to 4-year-old version of the SDQ (129). The total difficulties score will be used as general measure of child social adjustment/impairment. Parents will respond on a three-point scale, ranging from 0, *not true*, to 2, *certainly true*.

##### Disruptive Behaviors

At T4, the conduct problems subscale of the 2- to 4-year-old version of the SDQ (129) will be used to measure children's disruptive behaviors. At T3 and T4, disruptive behaviors will also be measured with items from Stringaris and Goodman (130) that have been previously used to index specific dimensions of oppositionality. This questionnaire will include 11 items that are rated on a three-point scale from 0, *not true*, to 2, *certainly true*; and three items that will be rated from 0, *never*, to 2, *often*.

##### CU Traits

At T4, mothers and fathers will report on their child's CU traits on the 24-item parent-report preschool version of the Inventory of Callous-Unemotional Traits (131). Parents will report on a four-point scale, ranging from 0, *not at all true*, to 3, *definitely true*.

##### Autism Symptoms

###### Modified Checklist for Autism in Toddlers

At T3, mothers and fathers will report child autism symptoms on the 20-item Modified Checklist for Autism in Toddlers [M-CHAT; (125)]. For each item, parents will respond either *no*, 0, or *yes*, 1.

###### Autism Spectrum Quotient

At T4, mothers and fathers will report child autism symptoms on the child version of the Autism Spectrum Quotient (132). Parents will respond to 10-items on a four-point scale, ranging from 1, *definitely disagree*, to 4, *definitely disagree*.

##### Anxiety Symptoms

At T4, mothers and fathers will report child anxiety symptoms on the 28-item Revised Preschool Anxiety Scale [PAS-R; (127)]. Parents will respond on a five-point scale, ranging from 0, *not true at all*, to 4, *very often true*.

##### ADHD Symptoms

At T4, mothers and fathers will report ADHD symptoms on the ADHD Rating Scales IV – Preschool version (133). Parents will respond on a four-point scale, ranging from 0, *never or rarely*, to 3, *very often*.

##### Child Mental Health Diagnoses

For those children scoring above the cut-off score on the SDQ or any of the parent-reported symptoms measured at T4, diagnostic interviews will be conducted. The Diagnostic Interview Schedule for Children (DISCAP) will be used to assess for DSM-5 diagnoses for child mental health disorders (134).

#### Data Analysis

The core design yields a set of repeated measures of the REAL constructs, and outcome indices of psychopathology. Latent growth variables for each of the REAL constructs will be developed for the longitudinal growth models. This produces a measurement model and starting points (intercept) and slopes for each measure and is important to ensure continuity of common variance of constructs over age changes. The outcomes variables will be used categorically as diagnoses, whereby category membership is the criterion variable and risk odds ratios are parsed into common variance (any psychopathology) and unique membership (such as the presence of ASD without concurrent diagnosis), and as continuous dimensional variables. Latent profile analyses will also be run to examine whether there is consistency in latent profiles across tasks relating to the REAL constructs. Further, the predictors and correlates of class membership will be examined. Latent transition analyses will also examine whether the group of individuals in each latent class based on REAL variables changes at each time point. Missing data will be examined for non-random patterns, and appropriate missing data strategies will be used to model any trends found. All analyses will be conducted using the contextual variables of environmental adversity and developmental progress/delay as covariates.

#### Sample Size

Longitudinal designs and growth modeling are notoriously difficult to assess for statistical power. The first consideration is for categorical analyses where power is generally the lowest as they split the sample into subgroups. We present power analyses in two ways. For predicting dimensions of psychopathology at T4 using regression, G*Power v3.1.9.2 shows the effect size detectable at power = 0.8, error = 0.05, 3 main predictors and 10 control variables, and a sample size of *N* = 450 shows we have the sensitivity to detect a small effect size of f2 =.024. For cross sectional categorical comparisons of psychopathology at the T4 assessment, the lowest power is available to test for ASD given it has the lowest expected base rate. Using G-power for Chi-squared tests with power = 0.8, significance at p=0.05, and a small effect size of w = 0.02, we require a total sample size of *N* = 321. Thus, the study is powered to detect the both categorical and dimensional tests of emerging psychopathology. Our final sample is *N* = 788 children (see **Figure 5**). Using the best available Australian and United States of America-European epidemiological studies to estimate the following numbers of children, it is estimated that the following full and at-risk diagnoses/profiles will be observed in the sample at T4: DBD-CU – full 10%, *n* = 79; at-risk 25%, *n* = 197); DBD+CU – full 6% *n* = 47, at-risk 15% *n* = 118; anxiety disorders – full 10% *n* = 79, at-risk 25% *n* = 197; ASD – full 1.5% *n* = 12, at-risk 8% *n* = 63. These are overlapping, non-mutually exclusive groups.

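### The categorical power claim does not hold for full ASD diagnosis: no base rate enters the calculation, the printed w and N disagree, and only about 12 cases are expected

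*Protocol article*

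**What the plan says.** The Sample Size section of the protocol article gives two power statements. For the dimensional outcomes at T4 it describes a regression with "3 main predictors and 10 control variables" at N = 450 and a detectable f2 of .024.

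For the categorical outcomes it chooses ASD as the limiting case, since "the lowest power is available to test for ASD given it has the lowest expected base rate". The calculation is a G*Power chi-squared test at 80% power and a 5% significance level. Its effect size is worded as "a small effect size of w = 0.02, we require a total sample size of", and the figure that the article then gives is 321 children. Degrees of freedom are not stated. The section then concludes that both kinds of test are adequately powered.

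The same section lists the cases expected at T4 among the 788 children recruited: "ASD – full 1.5% *n* = 12, at-risk 8% *n* = 63".

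The Data Analysis section plans to use diagnoses as criterion variables with odds ratios, split into any psychopathology and "unique membership (such as the presence of ASD without concurrent diagnosis"). It also plans to use the outcomes as continuous dimensions. All analyses carry covariates for environmental adversity and developmental progress or delay.

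**The concern.** The base rate is the stated reason for choosing ASD, yet the inputs are only w, alpha and power. A chi-squared sample size from w does not change whether the outcome affects 1.5% or 50% of children. The case named as hardest has therefore not been examined, although the section supplies the prevalence needed to do so.

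ASD appears in the first three hypotheses and is the only subject of the fifth. If the power claim is taken at face value, a null result at diagnosis level could be read as evidence against the REAL model when large effects could not be excluded. A positive result would rest on a handful of cases.

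**Working it through.** **Inputs from the protocol article.** Power 0.80, alpha 0.05, printed w = 0.02, stated N = 321; full ASD 1.5% and at-risk ASD 8% of 788; N = 450 and 3 + 10 predictors for the dimensional regression.

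**Assumptions.** Degrees of freedom are not given, so 1 to 6 were tried. N = 450 is not labelled as the T4 sample; it is used here as a lower scenario.

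**1. Reproducing the plan's figures.** N = λ / w², where λ is the noncentrality of the chi-squared test at the stated power and alpha (7.85 for df 1, 12.83 for df 5).

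| df | N for w = 0.02 | N for w = 0.2 |
|---|---|---|
| 1 | 19,623 | 197 |
| 2 | 24,087 | 241 |
| 3 | 27,257 | 273 |
| 4 | 29,839 | 299 |
| 5 | 32,070 | **321** |
| 6 | 34,061 | 341 |

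No choice of df gives 321 with the printed w. With w = 0.02, power at N = 788 is 6% to 9%. The stated N is matched exactly by w = 0.2 with df = 5, so a misprint of w is likely, and the rest of the check uses 0.2. The dimensional statement does reproduce: 3 tested of 13 predictors at N = 450 gives f2 = 0.0244.

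**2. Expected full ASD cases at 1.5%.**
- N = 321: 321 × 0.015 = 4.8. If df = 5 means six equal groups, that is 4.8 / 6 = 0.8 per group, too few for the chi-squared approximation.
- N = 788: 11.8, the article's 12. This allows for no attrition.
- N = 450: 6.75, about 7.
- For comparison, the attrition range quoted in the Discussion (6.4% to 49.9%) would leave 738 to 395 children, or about 11 to 6 cases.

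**3. What w = 0.2 means in a 2×2 comparison at p = 0.015.** With exposed share q ≥ p, the largest possible w is √[p(1−q) / (q(1−p))], reached when every case is exposed.
- 50/50: √(0.015/0.985) = 0.123
- 40/60: 0.151
- 1/3 vs 2/3: 0.175
- 25/75: 0.214

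So w = 0.2 cannot occur for the first three splits. At 25/75 the risks are p₁ = p + w√[p(1−p)]·√[(1−q)/q] = 0.015 + 0.2 × 0.1216 × 1.732 = 5.71%, and p₀ = 0.015 − 0.2 × 0.1216 × 0.577 = 0.096%. That is an odds ratio of about 63.

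**4. What the design can detect for full ASD.** For a mean difference, d at 80% power ≈ 2.80 × √(1/n₁ + 1/n₂).

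| | 12 vs 776 | 7 vs 443 |
|---|---|---|
| Detectable d | 0.82 | 1.07 |
| Power, d = 0.2 | 11% | 8% |
| Power, d = 0.5 | 40% | 26% |

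For a 2×2 Pearson test with exact binomial probabilities (lower figure 50/50, higher figure 20/80), power for an odds ratio of 3 is 38% to 47% at N = 788 and 23% to 34% at N = 450.

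**5. The odds-ratio models.** The article gives no predictor count for these. If there were five (three REAL predictors and one variable for each of the two covariate domains, an assumption), the ratio would be 7/5 = 1.4 to 12/5 = 2.4 cases per predictor. ASD without a concurrent diagnosis would have fewer cases still, since the article says the groups overlap and that ADHD often accompanies ASD.

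**6. At-risk ASD at 8%.** There are 36 (N = 450) to 63 (N = 788) cases. Here w = 0.2 corresponds to an odds ratio of about 4 to 6, and 80% power is reached at odds ratios of about 2.1 to 2.8.

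**The case against.** The best defence is that the ASD hypotheses do not depend on 12 diagnoses. The Data Analysis section already plans dimensional analyses, the Autism Spectrum Quotient is collected at T4, and the dimensional sensitivity figure is correct. The power sentence also says ASD without limiting it to full diagnosis, and at-risk ASD is workable at 8%. This stands, and it confines the problem to full diagnosis and the ASD-only contrast.

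Three stronger readings are tempting but not supported:

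- **That w = 0.2 is simply impossible at 1.5%.** The bounds in step 3 are for a 2×2 table, where w = 0.2 would give N = 197. N = 321 needs df = 5. With six equal groups the maximum w is √(5 × 0.015/0.985) = 0.276, so 0.2 is attainable there. The objection to that table is its sparse counts.
- **That the planned ASD models have fewer than one case per predictor.** That ratio (12/13 or 7/13) borrows the 13 predictors of the dimensional regression.
- **That a null ASD result would be meaningless, or that any logistic model would be separated or biased.** No estimator is named, and the dimensional results would still inform the ASD hypotheses. Estimator and covariate limits can properly be left to the analysis plan.

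**Conclusion.** The point holds for full ASD diagnosis. The article makes a positive power claim that its own prevalence contradicts, so this is not a detail left to another document. Two faults are certain from the text: the base rate given as the reason is not used, and w = 0.02 is incompatible with N = 321 at any df tried, by a factor of about 60 to 100 (19,623/321 = 61; 32,070/321 = 100).

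With 12 cases the smallest standardised difference detectable at 80% power is about 0.82, and a difference of 0.2 has about 11% power. These figures use the article's own expected count with no attrition. The worse figures (1.07 and 8%) assume that N = 450 is the T4 sample. Reading w as 0.2 is an inference from the exact match at df = 5.

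A reader might infer that the study is underpowered for ASD as a whole or for all categorical outcomes. The documents do not support that: at-risk ASD and the dimensional analyses have usable sensitivity, and the other diagnoses have higher expected rates and were not examined here.

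**What to change.** In the Sample Size section:
- correct w and state the degrees of freedom and the table that they refer to;
- restate the conclusion so that it excludes full ASD diagnosis, and give the detectable effect at the expected number of cases (about d = 0.82 with 12), with a figure after attrition.

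In the Data Analysis section:
- label full-diagnosis ASD comparisons and the ASD-only contrast descriptive or exploratory;
- make the T4 Autism Spectrum Quotient analysis (f2 = .024 at N = 450) primary for the ASD hypotheses, with at-risk ASD (8%, 63 children) as the categorical version.

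These are wording changes and data collection is unaffected. The cost is scientific: confirmatory claims at the level of ASD diagnosis are given up.

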**Figure 5 f5:**
[figure not shown]
Recruitment CONSORT Diagram.

## Discussion

In the model presented in this paper, it is argued that emotional attention, responsiveness, and learning (REAL) have the potential to explain common and unique variance in the early presentation of the common child psychopathologies of DBD-CU, DBD+CU, anxiety, ASD and ADHD. This study will be the first to test a clear developmental map of the REAL constructs and identify both the unique and specific causes of childhood psychopathology. The idea that REAL deficits are trans-diagnostic is consistent with the growing recognition that psychiatric disorders are not distinct categories but overlapping neurodevelopmental disorders (18). Healthy humans are born with exquisitely-tuned neural architecture for recognizing and attending to faces and eyes, and this underlies development of higher socio-emotional skills, conscience, theory of mind, empathy, and aspects of language and cognition (25, 34).

Early identification of impairments in this architecture can have clear and powerful implications for early assessment and treatment. For example, with regard to DBD, experimental manipulations of attention, whereby children with high CU traits and adults with psychopathic traits are trained to increase attention to emotional cues, are reliably associated with improved recognition, emotion, and learning in the presence of salient emotional stimuli (99, 135). Training attention away from emotional cues reduces fear in experimental manipulations and promotes positive coping in people with high anxiety and related disorders (36). In autism and DBD, training attention to the eyes can improve emotion recognition (136). These findings illustrate the potential treatment implications for the REAL constructs. It must be noted, however, that these empirical demonstrations are all with older children through to adults. It is reasonable to expect that effect sizes and the generalization of change will be considerably more impressive when they are targeted at young children during critical, or sensitive, periods for change. Thus, this study will identify more precise early intervention targets for children at risk for complex and comorbid conditions.

This study has a number of additional strengths. First, a large high-risk birth cohort will be recruited and followed for three years. Previous research using the same recruitment strategy in the same health district found that this strategy was ideal for over-sampling infants who were at high-risk for the development of mental health and developmental disorders (101). Second, by accessing reliable antenatal and birth data from participants' medical records, a range of antenatal and birth risk factors will be able to be examined and controlled. Thirdly, this study employs multi-method and multi-informant measures across time.

Although this study has several strengths, there are some limitations that must be noted. While the core features of DBD-CU, DBD+CU, excessive anxiety, ASD, and ADHD are all present and measurable by 3-years-old, there are problems with false-positives and false negatives. Unlike the other disorders, the diagnosis of ASD is relatively reliable by 3-years-old (137). There is however a proportion of children that will test positive for DBD (+/-CU), anxiety, and ADHD at 3-years-old but later desist (138). With anxiety disorders, the opposite problem may also be the case, as a substantial number of children develop a diagnosable anxiety disorder in late childhood and early adolescence. The evidence is clear that while these children may not have had a frank diagnosis at earlier ages, they will have shown long-standing problems with excessive fear, shyness, behavioral inhibition, and sensitivity, which are all traits that will be captured by our dimensional measures. False positive diagnoses and false negative diagnoses will be minimized by using multi-informant and multi-method assessment strategies that aim to produce diagnostics based on conservative and convergent data.

Another limitation is the risk of attrition. A review of longitudinal studies examining antenatal and postnatal depression found that attrition rates ranged from 6.4% - 49.9% across studies (139). Common features of non-completers across studies appeared to be mothers who were younger had lower socio-economic status, lower education, were unemployed, and those with higher depression scores (139). Although we have accounted for attrition in our power analyses, and have ensured a range of contact methods are available in order to reach our participating families over time (e.g., phone number, email address, mailing address, secondary contacts, etc.), it is possible that some families may be lost to follow up or choose to withdraw from the study. Further, it is possible that similar to other longitudinal studies, attrition may be selective. In order to assess the representativeness of the sample, we will compare key socio-demographic variables for those who drop out of the study compared to those who remain in the study at each time point.

Despite these concerns, this study has the potential to test a theoretical model of how precise variations in the REAL constructs lead to the most common childhood psychopathologies. It will help to identify the common and unique factors that underlie childhood mental health comorbidities and discrete disorders, respectively. Further, the study will identify critical variables and the developmental timings of these variables, as a road map for precise targets for early intervention for the prevalent childhood psychopathologies. Early detection of and intervention with the common childhood mental health disorders has the potential to alter adverse developmental trajectories in ways that are clinically significant for families and children, and socially and economically beneficial for communities.

## Ethics Statement

The studies involving human participants were reviewed and approved by The University of Sydney Human Research Ethics Committee (Project Number 2017/644), and the South Western Sydney Local Health District Human Research Ethics Committee (Local Project No HE17/115) have approved this study. Written informed consent was obtained from mothers for their participation and mothers also provided written informed consent for the participation of their child. Written informed consent was obtained from fathers for their participation.

